#### Later study exclusion criteria

Patients will be excluded from the study, if exclusion criteria occur during the intervention (e.g. cognitive impairments) or if patients show signs of acute suicidality (concrete thoughts and/or plans to commit suicide), in which case psychiatric care will be provided immediately. At the point of exclusion, study results up to this date and reasons for exclusion will be documented. These data will be further analyzed in the drop-out analysis.

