#### Study exclusion criteria

During the face-to-face interview the study research assistant evaluates the following exclusion criteria: (a) deficits in communication, (b) lack of willingness or inability to attend all of the necessary therapy sessions and (c) acute suicidality (concrete suicidal thoughts and/or plans, in which case psychiatric care is provided immediately). Patients who (d) score less than 20 points on the Short Orientation-Memory-Concentration test (SOMC) or (e) show a level of less than 70 on the Karnofsky index are excluded, because life expectancy in that case is expected to be less than 6 months [34, 35]. Patients will be further excluded from the study in case they receive parallel psychotherapy. Previous experiences with psychotherapy as well as concurrent psychopharmacological treatment are documented but are no reasons to be excluded from study participation.

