#### Statistical analysis

For the final analyses we will use an intention-to-treat approach (ITT) and compare patients in the assigned treatment groups. Main analyses to evaluate efficacy based on primary (depression) and secondary outcomes at 6 months follow-up (primary endpoint) will be performed using analysis of covariance (ANCOVA). In case of missing outcome data at the primary endpoint, we use the last observation carried forward (LOCF) method. Controlling for baseline test scores as well as demographic and disease-related characteristics, we hypothesize that the mean depression score in the IG will be lower than the one in the CG. Other analyses will include a mixed model approaches (to examine changes over time), regression analyses (controlling for additional factors), and exploratory analyses (of treatment effect modifiers).

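### Exclusion from the study after randomisation ends outcome collection for reasons tied to prognosis and depression, and the protocol does not reconcile this with its intention-to-treat analysis

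*Protocol article*

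**What the plan says.** Later study exclusion criteria sets a rule for patients who are already randomised: "Patients will be excluded from the study, if exclusion criteria occur during the intervention (e.g. cognitive impairments" is the first limb, and "or if patients show signs of acute suicidality (concrete thoughts and/or plans to commit suicide" is the second. On data it says: "At the point of exclusion, study results up to this date and reasons for exclusion will be documented". The next sentence gives the use: "These data will be further analyzed in the drop-out analysis". The main analysis is not mentioned there.

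The first limb refers to exclusion criteria in general and gives cognitive impairment only as an example. The list under Study exclusion criteria covers communication deficits, "lack of willingness or inability to attend all of the necessary therapy sessions", acute suicidality, a SOMC score below 20, a Karnofsky index below 70 (such patients "show a level of less than 70 on the Karnofsky index are excluded") and parallel psychotherapy. The article itself links the SOMC and Karnofsky limits to an expected survival of under 6 months.

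Statistical analysis states: "For the final analyses we will use an intention-to-treat approach (ITT) and compare patients in the assigned treatment groups". The primary endpoint is depression at 6 months, analysed by ANCOVA, with LOCF for a missing value at that time.

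Power calculation allows for 40% loss to follow-up and, separately, for 20% non-compliance. It assumes that non-compliant patients in the CALM arm respond like controls.

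**The concern.** ITT protects the randomised comparison only if patients are analysed as assigned and their outcomes are sought whatever happens after randomisation. Here a rule ends outcome collection after events that are themselves informative. Acute suicidality is closely related to depression, the primary outcome. Cognitive and functional decline are foreseeable in patients with stage III or IV disease and an average life expectancy of 12 to 18 months. The patients lost are therefore likely to differ from those who stay.

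The rule is worded identically for both arms, but its effect need not be. Therapists deliver only one of the two conditions, only the CALM therapists receive extra training, and CALM deals explicitly with mortality. How often suicidal thoughts come to light could therefore differ between arms. This is inference, not something the article reports, but it means that equal exclusion cannot simply be assumed. Questionnaires that were never sent cannot be recovered at the analysis stage.

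**Working it through.** **1. The plan's own sample size.** Inputs from Power calculation: r = 0.70, d = 0.405 (3 points with SD 7.4), completion p = 0.60, compliance c = 0.80. The article states neither alpha nor power; two-sided 5% and 80% are assumed here.

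- n = 2(1.960 + 0.842)² × (1 − 0.49) / 0.405² + 1 = 49.81, so 50 per group at 6 months.
- Recruitment: 50 / 0.60 / 0.80² = 130.2, so 131 per group and 262 in total.

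Both stated figures are reproduced. The point does not rest on an arithmetic error.

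**2. The two readings of the rule.**

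- *Strict.* The patient is out of the study and the data go to the drop-out analysis. The 6-month comparison then omits patients selected by an event after randomisation.
- *Lenient.* Study participation ends, but the patient stays in the assigned group and LOCF fills the 6-month value. By Table 1, and if earlier questionnaires were returned, the value carried forward is:

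| Time of exclusion | PHQ-9 | BDI-II |
|---|---|---|
| Before t1 (3 months) | screening value | none |
| Between t1 and t2 | t1 value | t1 value |

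Any value carried forward comes from before the event that led to exclusion. For the BDI-II, the scale behind the sample size, Table 1 shows no assessment before t1. The text under Baseline assessment implies that there is one, since it does not list the BDI-II among the measures left out of the baseline questionnaire. The article does not say which depression scale is primary.

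On both readings there is no observed 6-month outcome for these patients.

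**3. Possible size on the strict reading (assumed rates).** Let q be the fraction excluded in each arm and k the number of SDs by which excluded patients would have scored above those retained. Deleting them shifts the CALM minus control difference by −(q_CALM × k_CALM − q_control × k_control). With the same k in both arms:

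| q in the two arms | k | Shift (SD) | Shift (points, × 7.4) | Share of d = 0.405 |
|---|---|---|---|---|
| 5% and 5% | 0.5 or 1.0 | 0 | 0 | 0% |
| 10% and 5% | 0.5 | 0.05 × 0.5 = 0.025 | 0.19 | 6% |
| 10% and 5% | 1.0 | 0.05 × 1.0 = 0.05 | 0.37 | 12% |
| 15% and 5% | 1.0 | 0.10 × 1.0 = 0.10 | 0.74 | 25% |

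If CALM loses more patients, the shift favours CALM; if the control arm loses more, it hides a benefit. Equal rates do not guarantee zero: 10% in each arm with k = 0.5 in one and 1.0 in the other gives 0.10 × 0.5 = 0.05 SD. None of these rates or excesses comes from the article.

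**4. Link to the non-compliance factor.** The 1/c² term presupposes that non-compliers stay in the comparison and dilute the effect. If they were removed, recruitment would be 50 / 0.60 / 0.80 = 104.2, so 105 per group rather than 131. A conflict with the sample size arises only if the attendance criterion is also applied after randomisation.

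**The case against.** A reader might infer that the plan deletes these patients from the main analysis and so contradicts ITT outright. The text does not go that far. The word further in "These data will be further analyzed in the drop-out analysis" can mean an additional analysis. Exclusion from the study can mean the end of participation, and Statistical analysis retains patients by assigned group with LOCF. No section says that excluded patients are left out, and none says that they are kept. This part of the objection stands: it is a tension, not a proven contradiction.

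A reader might also infer a contradiction with the sample size. Later exclusions fit within the planned 40% loss to follow-up. The attendance criterion is introduced as something judged at the face-to-face interview, therapy is up to eight sessions, and the later rule names only cognitive impairment and suicidality. Table 1 schedules the SOMC only at screening and lists no repeat Karnofsky rating. The broad reading is literally possible but has no scheduled check behind it, so this conflict is conditional.

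Finally, this is a condensed article, and the definition of the ITT set may stand in a fuller document. That would answer a complaint about a missing definition. It does not answer a stated rule that ends outcome data at exclusion. LOCF does not answer it either, for the reasons shown in the table of carried values.

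**Conclusion.** The point holds as a tension that needs reconciling. The rule on later exclusions ends data collection for reasons tied to prognosis and to the depression outcome, and it sits badly beside an ITT analysis at 6 months. Selective loss of 6-month outcomes follows on either reading; removal from the ITT set follows only on the strict one.

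The size and direction of bias are unknown. Bias arises if exclusion rates, or the outcomes of those excluded, differ between arms, and the article gives no information on either. The 0.19 to 0.74 points (6% to 25% of the target effect) are illustrations that assume unequal rates and full deletion. A reader might take them to show a bias in favour of CALM; the documents support neither that direction nor that size. The conflict with the 1/c² inflation applies only if the attendance criterion is used after randomisation.

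**What to change.** Reconcile Later study exclusion criteria with Statistical analysis and Power calculation by stating that:

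- a later exclusion does not remove a patient from the ITT set or from the assigned group;
- t1 and t2 outcomes continue to be collected unless consent is withdrawn, the patient cannot validly complete them, or the responsible clinician judges contact inappropriate;
- all observed values enter the primary analysis;
- remaining gaps are treated as missing data, with a sensitivity analysis that does not rely on LOCF;
- later exclusions and their reasons are reported by arm.

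The text should also say whether the attendance criterion applies after randomisation, because the 131 per group presupposes that non-compliers are retained. The rules on study therapy and psychiatric care are left as they stand.

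The cost is a change of wording and some additional follow-up contact, using questionnaires and reminders already in place. Some questionnaires will be of limited validity, for example after new cognitive impairment, and some will not be obtainable.

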### Randomization procedure

Study participants are randomly assigned to receive either CALM or SPI. The random allocation sequence (randomization list) was generated by the Institute of Medical Biometry and Epidemiology at the University Medical Center Hamburg-Eppendorf. Randomization is stratified according to sex. After a patient gives written informed consent for study participation, a study research assistant reports the patients’ initials, date of birth and sex to a blinded research assistant at the University Medical Center in Leipzig. The research assistant includes the patient in the randomization list and informs the research assistant about treatment allocation (CALM or SPI). No CALM study member and research assistant has access to the randomization list. The patient is not informed about their treatment condition.

### Assessment

#### Baseline assessment

The baseline questionnaire (t_0_) is handed to the patient by the research assistant at the end of the face-to-face interview and includes all primary and secondary outcome measures, except for the PHQ-9 depression inventory and the Distress Thermometer, which have been used as screening instruments to assess eligibility prior to the interview, and the GAD-7 anxiety inventory (Table 1).

**Table 1 Tab1:** Study measures

			t_0_	t_1_	t_2_
		Screening/face-to-face interview	(baseline)	(3 months follow-up)	(6 months follow-up)
Demographic characteristics		X			
Medical and treatment-related characteristics		X		X	X
Short Orientation-Memory-Concentration test	(SOMC)	X			
Structured Clinical Interview for DSM Disorders: Major Depressive Disorder Module	(SCID–I)	X			
Distress Thermometer	(DT)	X		X	X
Depression module of the Patient Health Questionnaire	(PHQ–9)	X		X	X
Beck Depression-Inventory II	(BDI–II)			X	X
Generalized Anxiety Disorder Questionnaire	(GAD–7)	X		X	X
Demoralization Scale	(DS)		X	X	X
Brief Fatigue Inventory	(BFI)		X	X	X
Memorial Symptom Assessment Scale Short Form	(MSAS–SF)		X	X	X
Functional Assessment of Chronic Illness Therapy-Spiritual Well-Being Scale	(FACIT–SP)		X	X	X
Death and Dying Distress Scale	(DADDS)		X	X	X
Posttraumatic Growth Inventory	(PTGI)		X	X	X
The Experience in Close Relationships InventoryModified Short Term Version	(ECR–M16)		X	X	X
Quality of Life at the End of Life Cancer	(QUAL–EC)		X	X	X
Couple Communication Scale	(CCS)		X	X	X
Clinical Evaluation Questionnaire			after every therapy session		

#### Follow-up assessments

Two follow-up assessments are realized at three (t_1_) and 6 months (t_2_) following the baseline assessment. The follow-up assessments ideally correspond with the completion of the third or fourth and the sixth to eighth CALM therapy session. Participants receive the study questionnaires with a prepaid envelope and are asked to return them within 2 weeks. Those have not returned the study questionnaires within 2 weeks receive a reminder. If patients do not reply within one week after the reminder, the study research assistant will contact them by phone. The follow-up measures include the assessment of changes in demographics as well as medical and treatment-related events (e. g. new diagnoses or complications, hospitalization in the past 3 months, whether patient signed a living-will in the past 3 months) and other significant life events.

#### Evaluation of individual therapy sessions

Following each CALM or SPI therapy session, patients and therapists complete the Clinical Evaluation Questionnaire [36]. This questionnaire measures to what extent patients perceived their therapy session as helpful, and to what extent therapists felt they were supportive to the relevant aspects.

Both treatment conditions (IG and CG) end after 6 months and a maximum of eight sessions. Therefore, the last outcome assessment of the study takes place after 6 months and a maximum of eight sessions. If there is a further need for psychosocial support we offer participants the possibility to receive further treatment after study completion – either by their study therapist or a newly assigned one, according to capacity.

### Quality standards and therapists training

#### The CALM treatment manual

We translated and adapted the CALM treatment manual [37] into the German language.

#### Therapist qualifications

Our study therapists are certified psychologists with additional psycho-oncological and/or psychotherapeutic training. All study therapists are pair-randomized to the treatment conditions (IG and CG) to minimize a possible bias.

#### CALM training

CALM therapists receive a comprehensive CALM training at each study center in Hamburg or Leipzig. Therapists randomized to the control condition do not receive any additional training.

#### Supervision

To ensure the quality of the therapy under both treatment conditions, both CALM and SPI therapists receive regular supervision by experienced supervisors in separate groups. The supervisor of the IG has received the same comprehensive CALM training.

#### Tape recording

Every therapy session in both treatment conditions is audio taped. Our research team will analyze audio recordings of randomly selected therapy sessions to evaluate treatments regarding process quality.

### Main study hypotheses

We hypothesize that patients in the CALM intervention will show a significantly lower level of depression 6 months after baseline compared to patients in the control group (SPI). We further hypothesize a significant reduction in anxiety and fatigue as well as significant improvements in psychological and spiritual well-being, meaning and post-traumatic growth in the CALM intervention compared to SPI 6 months after baseline.

### Measures

Table 1 shows all study measures included in our CALM RCT. We are collecting demographic information (e. g. age, sex, marital status, education, occupational situation) through a standardized questionnaire as well as medical and treatment-related variables (e. g. cancer diagnosis, date of diagnosis, past and current medical treatments) through medical charts.

The *Short Orientation-Memory-Concentration test* (SOMC) [31, 32] is a validated culture-fair instrument for assessing orientation, memory and concentration. The SOMC scores range from 0 to 28. Scores less than 20 indicate cognitive impairments.

The *Structured Clinical Interview for DSM-IV (SCID-I)* [33] is a valid structured interview and the gold standard for assessing DSM-IV Axis I disorders. We use the 15 items representing the DSM criteria for a *major depressive disorder* in the face-to-face interview to screen whether patients meet the criteria for a major depressive disorder. The interviewer evaluates to what extent a patient’s answers meet the depression criteria from one (criterion not met) to three (criterion is fully met). To diagnose a major depressive episode at least five out of nine symptoms need to be scored with 3, one being item 1 or 2.

The German version of the *Distress Thermometer (DT)* [30] is a valid and reliable self-report instrument for screening psychological distress in cancer patients. The single-item visual analogue scale ranges from 0 (no distress) to 10 (extreme distress) to quantify the global level of distress and is accompanied by a standardized symptom checklist. In our RCT, only the single-item visual analogue scale is used. Scores equal to or higher than five indicate significant psychological distress.

The *Depression module of the Patient Health Questionnaire (PHQ-9)* [27–29] is a valid self-report screening instrument for depression. It includes nine items, which reflect the DSM-IV criteria for major depression. Items are scored on a four-point Likert scale from 0 (not at all) to 3 (nearly every day) with a total score ranging from 0 to 27. Scores up to four indicate absence of depression, scores from five to nine indicate mild depression, scores from 10 to 15 indicate moderate depression, and scores higher than 15 indicate severe levels of depression [38]. The German adaptation of the instrument shows high internal consistency with Cronbach’s α = .89 [39].

The *Beck Depression-Inventory II (BDI-II)* [40] is a valid self-report questionnaire evaluating the severity of depression. The measure consists of 21 items, which reflect the DSM-IV symptom criteria for a major depressive disorder. Items are scored on a four-point Likert-scale rated from 0 (I don’t feel particularly guilty) to 3 (I feel guilty all of the time) with a total score ranging from 0 to 63. Scores up to 13 indicate none or minimal depression, scores from 14 to 19 indicate mild depression, scores from 20 to 28 indicate moderate depression and scores higher than 29 indicate severe depression. The German BDI-II version [40] shows high internal consistency with Cronbach’s α ≥.84 for various samples [41].

The *Generalized Anxiety Disorder Questionnaire (GAD-7)* [42, 43] is a brief self-report questionnaire assessing generalized anxiety disorder. It includes seven items, which reflect the DSM-IV symptom criteria for generalized anxiety disorder. Items are scored on a four-point Likert scale ranging from 0 (not at all) to 3 (nearly every day) with a total score ranging from 0 to 21. Scores up to 4 indicate absence of anxiety, scores from 5 to 9 indicate mild anxiety, scores from 10 to 15 indicate moderate anxiety, and scores higher than15 indicate severe levels of anxiety. The German adaptation of the instrument shows high internal consistency with Cronbach’s α = .89.

The *German version of the Demoralization Scale (DS)* [44, 45] is a validated self-report instrument measuring demoralization [46]. The scale includes 24 items representing four subscales: loss of meaning and purpose, dysphoria, disheartenment and sense of failure. Items are scored on a five-point Likert scale ranging from 0 (never) to 4 (all the time) with a total score ranging from 0 to 96. Scores less than or equal to 30 indicate low demoralization whereas a score greater than 30 indicate high demoralization. The German version shows high internal consistency with Cronbach’s α = 0.84 [45].

The *Brief Fatigue Inventory (BFI)* [47, 48] is a short, validated instrument for assessing the severity of fatigue in cancer patients. After patients stated whether they felt unusually tired or fatigued during the past week, nine items measure experienced fatigue as well as its interference with certain aspects of patients’ lives within the last 24 h. Fatigue is rated on an eleven-point Likert-scale from 0 (no fatigue/does not interfere) to 10 (as bad as you can imagine/completely interferes). The mean BFI score is calculated from the nine items, with 1–4 indicating mild, 5–6 moderate and 7–10 severe fatigue. The German version shows high internal consistency with Cronbach’s α = 0.92 [48].

The *Memorial Symptom Assessment Scale (MSAS)* [49, 50] is a validated self-report instrument assessing the number of physical problems that may occur as a result of cancer or its treatment. For our study we use the list of symptoms suggested by Chang et al. [50] in their adapted version (MSAS-Short Form). The MSAS-SF assesses symptom frequency and resulting distress only. Items are scored on a five-point Likert-scale ranging from 0 (not at all) to 4 (very much). The average symptom score is calculated. The scale shows high internal consistency with Cronbach’s α = 0.87. We did not include the four psychological items of the MSAS-SF in our study because we assess psychological symptoms using other validated instruments.

The German version of the *Functional Assessment of Chronic Illness Therapy-Spiritual Well-Being Scale (FACIT-SP)* [51] is part of the FACIT measurement system. The self-report instrument measures in what way spirituality and religion contribute to the quality of life of cancer patients on the two subscales meaning/peace and faith. Items are scored on a five-point Likert-scale from 0 (not at all) to 4 (very much) with a total score ranging from 0 to 48, high scores indicating higher spiritual well-being. Subscales and the sum score show high internal consistency with Cronbach’s α = .80.

The *Death and Dying Distress Scale (DADDS)* [52, 53] is a self-report instrument assessing specific concerns of advanced cancer patients concerning insecurity about ones end of life, being a burden to others, as well as lost time and opportunities. The German adaptation includes nine instead of 15 items. Additionally, the Likert-scale was changed from a six-point to a five-point Likert-scale with mild and moderate distress put together to one label. Items can be scored from 0 (no distress) to 4 (very much distress), resulting in a sum score from 0 to 36, a higher score indicating higher distress.

The *German version of the Posttraumatic Growth Inventory (PTGI)* [54, 55] is a self-report instrument assessing personal posttraumatic growth after a traumatic event. It consists of 21 items representing four subscales: new possibilities, relating to others, appreciation of life and spiritual change. Patients are asked if their life changed because of their cancer diagnosis. Items are scored on a three-point Likert-scale ranging from 0 (not at all) to 2 (very much) with a total score ranging from 0 to 42, a high score indicating high posttraumatic growth. The German version shows high internal consistency with Cronbach’s α = 0.92 [55].

The *Experiences in Close Relationships Scale (ECR-M16)* [56, 57] is a self-report instrument assessing patients’ experiences in close romantic as well as non-romantic relationships on two subscales anxiety and avoidance. It is a shorter version of the ECR-36 [56] including 16 items due to usage in groups of highly distressed patients. Items are scored on a seven-point Likert-scale ranging from 1 (disagree) to 7 (agree) with a total score ranging from 16 to 56 on each subscale. Higher scores on one or both subscales indicate high attachment insecurity. Both subscales show high internal consistency with Cronbach’s α = 0.91 (anxiety) and α = 0.88 (avoidance) [57].

The *Quality of Life at the End of Life Cancer (QUAL-EC)* [58] is a self-report instrument assessing quality of life in patients at the end of their lives regarding their perception of a good death. The instrument includes five subscales: symptom control, relationship with health care provider, preparation for end of life and life completion. It includes 17 items, the first three items measuring symptom control and referring to three physical or emotional symptoms the patient has to name at the beginning. We used items 4–17 measuring the remaining three subscales. Items are scored on a five-point Likert-scale ranging from 1 (not at all) to 5 (completely) with a total score ranging from 14 to 70, high scores indicating high quality of life. The instrument shows high internal consistency with Cronbach’s α = 0.83.

The *Couple Communication Scale (CCS)* [59] is an online-measure for assessing communication, conflict solution and relationship satisfaction in romantic relationships and was developed as a part of the ENRICH/PREPARE program [60]. The scale is part of the Couple Checkup Scale which includes 32 items covering – depending on relationship status (dating, engaged, married) – different aspects of romantic relationships that were found to be important for a happy marriage. In accordance with [name] and colleagues we only used the ten items depicting communication in romantic relationships in our study. Items can be scored from 1 (strongly disagree) to 5 (strongly agree).

The *Clinical Evaluation Questionnaire* [36] is a self-report seven-item questionnaire assessing the extent to which a therapeutic session was perceived as helpful for patients on such dimensions as being able to discuss their concerns about cancer and their treatment options and to clarify their values. The questionnaire is answered on a five-point Likert scale, ranging from 0 (not at all) to 4 (very much). Higher values indicate a higher degree of perceived benefit. If a certain aspect is not relevant, items can be rated as not applicable.

In case there was no German adaptation of the instrument available, we used state-of-the-art forward- back-translation by two independent research assistants.

